### 2.5.2. Medical Record Abstraction

The following variables will be abstracted from the medical records at week -2 (study entry): child diagnosis, cancer-directed treatments, and symptom treatments.

From week 0 to 16 (i.e. randomization point to end of follow-up), information will be abstracted every four weeks by RCs summarizing events that occurred in the four-week window including: disease status (stable, progression, remission), date of change in status when appropriate, cancer-directed and symptom treatments, formal PC referrals, hospitalizations, No. of psychosocial clinician encounters and No. of PC encounters documented. Chart abstraction forms will be entered into PediQUEST web.

### 2.5.3. Exit interviews

Children 8 years old or older who completed data collection through week 16 (end of follow-up) or dropped out and their parents, and parents of patients who died will be invited to participate in an exit in-depth interview to understand more about their experience in the study. The interview will be administered by the RC by phone, or face-to-face, and audio-recorded. The exit interviews will ideally take place within a week of answering the last PediQUEST Surveys. If this is not feasible, RC will schedule it at the next most convenient time. In addition, a sample of approximately 18 oncology providers per site will participate in exit interviews after their patient completes the study. A convenient sample of PC providers will be interviewed throughout the study.

The goal of these interviews is to collect information that will help understand **processes (of the study and of care)** in both arms and **intervention delivery/fidelity in intervention arm**, as well as identify the “active ingredients” of the intervention, and potential for adoption and dissemination (See Appendix-Study Instruments). Key topics to be addressed: reasons for participation, burden/facilitators to keep participating, symptom processes, and in the case of participants in intervention arm, intervention delivery, and potential for adoption (characteristics, likes/dislikes).

When a participant communicates the decision to drop out, the RC will ask permission to record and conduct a brief exit interview mainly focused on understanding reasons for dropout. If participant agrees, will discuss about the other topics mentioned above (symptom processes and intervention delivery if participant was on intervention arm).

If the patient died during the study, the research coordinator will send a letter (see Appendix-Recruitment Materials section) to the parents 12 weeks after the death to invite them to participate in a phone or face-to-face interview. The letter will contain an opt-out card. Parents will be instructed to return the opt-out card if they are unwilling to participate in the survey. Parents who do not return the opt-out card will receive up to three follow-up telephone calls by an investigator, with a maximum of two phone messages left, starting approximately a week after the letter is sent and repeated weekly to ascertain whether or not they have received the letter. If they have not received the letter, the researcher will ask if they are willing to receive it and will verify the mailing address. If parents agree to take part, the RC will schedule a convenient time to

conduct the exit interview and discuss whether they prefer to do it by phone or in person (at the clinic or hospital). Parents who do not send back the opt-out card and are unreachable by phone will be considered a refusal to participate. In the exit interviews, in addition to the key topics mentioned above, parents will also be prompted to provide their perspective on end of life care.

## 2.6. Sample Size

The target sample size (SS) is N=136 participants 68 in each arm. Texas Children's Hospital will have a slightly lower accrual goal of 34 total dyads, as opposed to 50 dyads, since they will collect data for a shorter period of time. Based on prior work, we estimate that there will be approximately 32 eligible patients/site/year, representing a total of 288 eligible patients over the 36 months the study will be available for recruitment. Pilot data suggest an enrollment rate of 70% which translates into approximately 200 patient-parent dyads, our enrollment target. After the two-week run-in period, non-responders will be excluded. Assuming that about 25% will be non-responders, a conservative estimate based on pilot data, there would remain 150 patients to be randomized to either the intervention (n=75) or usual cancer care (control, n=75). Based on previous work we estimate an attrition of approximately 10%, mainly due to dropouts. We therefore expect to collect complete data on a minimum of 136 dyads, 68 per group, a sample size that achieves sufficient power for all outcomes.

### 2.6.1. Power considerations

Although the SS is mainly driven by pragmatic considerations (target population is small), power calculations were conducted and indicate that our projected minimal SS of 68 children per group provide sufficient power for both primary and secondary outcomes for clinically meaningful effect sizes. All power calculations presented below were computed with two sample independent one-side tests,  $\alpha=0.05$  unless otherwise specified. For Aims 1 and 2 power estimates are conservative because they only use one observation per subject (average across time) without accounting for the repeated measures within subject.

*Aim 1 HRQoL (primary) and Symptom (secondary) outcomes:* Standard deviations for these outcomes were estimated using data from our PQ study (39 weeks follow up, surveys answered when attending clinic or once a month). For each child, we identified all 16-w periods with  $\geq 6$  surveys and calculated mean PedsQL total and mean PQ-MSAS total scores for each 16-w period. We randomly selected one period per child and estimated the standard deviation of 16-week PedsQL means (SD). Strategy was repeated 10 times and a pooled estimate was calculated. A sample size of 136 children (68 per group) achieves 85% power to detect a 4.4 point increase (MCID) in the mean over 16-w PedsQL Total score (SD for both groups 9.5), and a 95% power to detect a 3-point decrease in mean over 16-w PQ-MSAS total score (SD = 5.3). These power calculations are conservative as they are based on mixed responses coming from parents and children, while in the current proposal responses from different informants will be considered in separate analyses and are expected to have less variability.

*Aim 2 Parental anxiety (S-TAI-State), and depression (CES-D-10) (secondary outcomes):* A sample size of 68 parents per group achieves more than 80% power to detect a moderate to large effect size (Cohen's  $d = 0.43$ ). For example, this effect size would correspond to a difference of 5.2 points in mean S-TAI-State (SD=12.2).

Aim 3 Family Activation outcomes (secondary outcomes): Change in parent activation level between baseline and 16-w. The target sample size achieves 80% power to detect a change in any of the coping scale scores of size 0.5. This effect sizes correspond, for example, to a score change of 0.75 points between baseline and 16-w (estimating a SD = 1.5, consistent with literature reports). The sample size has 82% power to detect a mean increase of 2 encounters with psychosocial clinicians between trial arms in 16-w (SD=4.5, from pilot data). Finally, for mean No. of CT used for symptom treatment over 16-w, our sample size has 80% power to detect an effect size of 0.43.

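### The 80% power stated for a 0.5 SD change on the Brief-COPE scales does not follow from 68 per arm and the declared one-sided 5% test, which give about 90%

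*Protocol*

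**What the plan says.** Section 2.6 of the Protocol fixes the analysed sample: "The target sample size (SS) is N=136 participants 68 in each arm". Section 2.6.1 then sets a common rule: "All power calculations presented below were computed with two sample independent one-side tests", at alpha 0.05 unless something else is specified.

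For Aim 3 the section makes three statements at this sample size:

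- **Brief-COPE scales:** "The target sample size achieves 80% power to detect a change in any of the coping scale scores of size 0.5". This is illustrated as "a score change of 0.75 points between baseline and 16-w", "estimating a SD = 1.5, consistent with literature reports".
- **Psychosocial encounters:** "The sample size has 82% power to detect a mean increase of 2 encounters with psychosocial clinicians between trial arms in 16-w", with an SD of 4.5.
- **Complementary therapies:** "our sample size has 80% power to detect an effect size of 0.43".

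No other alpha, sidedness, test or sample size is given for the coping scales. The only multiplicity rule, in section 4.3.1, is a False Discovery Rate correction for analyses that were not planned. It does not cover these hypothesised outcomes.

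**The concern.** With the sample size, alpha and test fixed, power rises with the standardised effect. The Aim 3 paragraph nevertheless gives 80% at 0.43 SD, 82% at 2/4.5 = 0.444 SD and 80% again at 0.5 SD. One common test cannot produce all three. The unit is not in doubt, because 0.75/1.5 = 0.5 shows that the 0.5 is in SD units.

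The three coping scales carry hypothesis H3. If the declared rule holds, the smallest difference detectable with 80% power is overstated. If another test, alpha or SD was used, the protocol does not say so. An undeclared alpha or sidedness would also affect how the coping results should be read.

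**Working it through.** **Inputs** (Protocol 2.6 and 2.6.1): n = 68 per arm; one-sided alpha 0.05, so z = 1.645; effects and SDs as stated for each outcome.

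**Formula** (normal approximation): power = Φ(d·√(n/2) − z), with √(68/2) = 5.831. The noncentral t result is given beside it.

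**Step 1. Reproduce the section's figures under the declared rule.**

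| Outcome | d | Stated | Normal | Noncentral t |
|---|---|---|---|---|
| PedsQL total | 4.4/9.5 = 0.463 | 85% | 85.5% | 85.1% |
| PQ-MSAS total | 3/5.3 = 0.566 | 95% | 95.1% | 94.9% |
| Parent anxiety, depression | 0.43 | more than 80% | 80.6% | 80.2% |
| Psychosocial encounters | 2/4.5 = 0.444 | 82% | 82.8% | 82.5% |
| Complementary therapies | 0.43 | 80% | 80.6% | 80.2% |
| **Brief-COPE scales** | **0.75/1.5 = 0.5** | **80%** | **89.8%** | **89.5%** |

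For Brief-COPE: 0.5 × 5.831 − 1.645 = 1.271, and Φ(1.271) = 0.898. The other rows agree with the stated values to within a point. This row is off by about 9.5 points, so rounding or choice of software does not explain it.

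**Step 2. Find the effect that has 80% power.** d = (1.645 + 0.842) × √(2/68) = 0.426, which rounds to 0.43. In points this is 0.426 × 1.5 = 0.64. The stated 0.75 is larger by a factor of 0.75/0.64 = 1.17. Conversely, 80% power at 0.5 SD needs only 50 per arm (51 by the t-test).

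**Step 3. Try other assumptions.** None of these is stated in the protocol for the coping scales.

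| Variant at d = 0.5, 68 per arm | Normal | Noncentral t |
|---|---|---|
| Two-sided 0.05 | 83.0% | 82.5% |
| One-sided 0.05/3 (three scales) | 78.5% | 77.7% |
| One-sided rank test, assumed efficiency 0.955 | 88.6% | – |
| Two-sided rank test, assumed efficiency 0.955 | 81.3% | – |

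Using the 75 per arm expected at randomization instead of 68 moves the figure further away: 92.2% one-sided and 86.5% two-sided.

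The SD of 1.5 might instead describe a single score. The SD of change is then 1.5 × √(2(1 − ρ)), where ρ is the correlation between baseline and week 16. The protocol gives no ρ. Assuming ρ = 0.3, 0.4 or 0.5, the change SD is 1.77, 1.64 or 1.50, and one-sided power for 0.75 points is 79.4%, 84.5% or 89.8%. A ρ near 0.3 would bring power for 0.75 points close to 80%, but the effect would then be 0.75/1.77 = 0.42 SD. That contradicts the protocol's own conversion to 0.5.

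**The case against.** The strongest reply is that nothing rests on this figure. The sample gives more power for 0.5 SD than claimed, the scales are secondary outcomes, and section 2.6.1 says that the sample size was set mainly on pragmatic grounds. Read as a floor, 80% power for 0.5 SD is true, and two floors for two different outcomes do not contradict each other. The section's wording is also loose: for the same d of 0.43 it writes "A sample size of 68 parents per group achieves more than 80% power to detect a moderate to large effect size" in one place and a plain 80% in another. Finally, section 2.4.2.2 calls the coping changes ordinal and section 4.3.2.3 leaves the link and distribution open, so a rank-type calculation is conceivable.

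The point about consequence stands. The floor reading is weak, because the other figures in the section are close to exact and a reader would take 0.75 points as the difference detectable at 80%. A rank test on the declared one-sided basis still gives about 86 to 89% (assumed efficiency 0.864 to 0.955), so it does not rescue the figure. It is fair to add that the origin of the 80% cannot be established. Two-sided testing, an alpha split, a rank test, a different SD or simple rounding to a conventional value are all possible, and no hidden test should be inferred.

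**Conclusion.** The concern holds. Under the sample size, test and alpha that the protocol declares, power at 0.5 SD is about 90%, not 80%, and 80% power corresponds to about 0.43 SD (0.64 points). The sentence is also incompatible with the 82% and 80% figures beside it under any one common test. This rests on three readings of the protocol: 68 analysed per arm, the one-sided 5% rule applying to the coping scales because no exception is stated, and 1.5 being the SD of the change. The error is minor and conservative. The sample size and the claim of sufficient power are unaffected.

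**What to change.** Rewrite the one sentence so that it matches the calculation behind it.

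- **If the declared test applies:** state either 80% power for 0.43 SD (0.64 points at SD 1.5) or about 89% power for 0.5 SD (0.75 points).
- **If another test was used:** name it and give its power at 0.5 SD, about 82% for a two-sided 5% test or about 78% for a one-sided test with alpha split over the three scales.
- **If 1.5 is the SD of a single score:** give the correlation assumed and restate the effect size in SD-of-change units.

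The cost is one corrected sentence. The sample size and the analysis need no change.

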## 2.7. Recruitment

We will recruit consecutive patients at each of the outpatient oncology clinics or inpatient wards of the five participating sites or remotely. Based on prior work, we expect to enroll between 1-2 patients/site/month; considering that the target population is 23-34 patient-parent dyads/site and that enrollment rates will vary over time, we presume that the enrollment period will last approximately 27 months/site and the data collection period an additional four months. Recruitment will start in a staggered fashion, adding a new site every three months, ending with a total enrollment time of 36 months across the five sites (see section 7, Study timeline). We will enroll one parent per patient, as designated by the family, recommending that it be the parent who holds more of the primary caregiving role.

For all eligible patients, the recruitment protocol will be similar to that used in our prior prospective study and pilot. At each center, RCs will generate a list of potentially eligible patients by reviewing clinic rosters and e-mail sign-outs on a daily basis, establishing direct communication with primary oncology teams, and attending clinic and tumor board conferences. When we reach a plateau in identifying new patients, clinic roster and sign-out screen will be conducted on a weekly basis. Study promotion activities will consist of short in-service meetings at study launch ((with additional meetings conducted later if recruitment is low).

To generate the list of potentially eligible patients, all patients belonging to the *base population* (see section 2.2.1), i.e.  $\geq 2$  years old AND seen by the outpatient oncology clinic or inpatient oncology service will be entered into a *pool list* excel file. The *pool list* file will have automated fields and allow for a quick pre-screening process that renders a patient either potentially eligible or not eligible. For all patients identified as potentially eligible, RCs will proceed to screening using the “Eligibility Form” in REDCap, and eligibility will be verified by reviewing patient’s medical chart (Appendix-Recruitment Materials) and validated by a designated investigator. Investigator will send an email through REDCap to RC confirming patient’s eligibility status. After eligibility is verified by the local PI, RCs will collect potential participant’s contact information, race/ethnicity, English proficiency, and main diagnosis from the medical record. This data will be entered on the “Subject and contact information form” in REDCap to help the approach process and better understand selection bias. In order to monitor the identification and pre-screening process, every two months, the PI will review medical records of 5% of participants identified as not eligible during the pre-screening phase. If the error rate is larger than 5%, RCs will be re-trained and participants screened again.

A HIPAA waiver is requested for the whole identification process (see section 6.2.2). The RC will then email the primary oncologist (MD or nurse practitioner) to inform him/her that the RC will approach the patient during

the next visit, giving the provider the opportunity to refuse the approach (See email template in Appendix- Recruitment Materials). RC will register the provider opt-out process outcome in REDCap.

The RC will next approach the family when in clinic or on the ward, if the patient is admitted, and will provide a brief overview of the study, will hand the parent and patient age-appropriate study brochures (see Appendix- Recruitment Materials), and conduct a tablet demonstration of PQ web. If families are interested in participating, the RC will move forward with the consent process providing more details or schedule a convenient time to do so. If preferable for the family, this second conversation may take place over the phone and the family may bring a completed copy of their consent form to their next visit. If after being introduced to the study and having had the opportunity to ask questions, the child and parent(s) are willing to participate, the parent and patient if older than 10 years of age will be asked to review and sign the informed permission/ assent documents covering the patient's participation (more details in section 6.2). A separate consent document will cover caregiver's participation. If families do not make a decision right away, the RC will develop a follow-up plan with the family. All the approach process will be documented in REDCap's "Approach Form." If more than a week has elapsed, disease-related eligibility criteria will be re-verified.

In addition to in-person recruitment, the RC may also conduct the consent process remotely. For these procedures, email addresses, mailing addresses, and phone numbers will be obtained from the patient's medical record. Eligible participants will be mailed or emailed an information sheet that outlines the details of the study and elements of informed consent, along with study brochures and an opt-out opportunity. If a participant decides to opt-out, they will be prompted to answer a non-participant questionnaire within the document for opt-out instructions. If no opt-out occurs, the RC will then follow up with a phone call after a few days to ensure that the documents have been received and gauge the family's interest in learning more. If the family declines participation, they will be prompted to complete the non-participant questionnaire verbally over the phone. If the RC has maximized outreach attempts to enroll the family, at this point they will be classified as a passive decline and will be asked to complete the non-participant survey. These 'passive declines' will receive a unique opt-out document with language specific to their situations. If the family expresses interest in participating, the RC will provide details on the study, walk through the consent form to ensure that all elements of informed consent are provided, and offer the family the opportunity to ask questions. If the parent and child (when applicable by age) decide to participate, they will be sent the appropriate consent/assent documents to sign and return via mail or email. Alternatively, parents and children can also provide verbal consent/assent in place of written documentation of informed consent. In cases of verbal consent/assent, parents and children older than 18 will provide verbal consent. Children older than 10 but younger than 18 will provide verbal assent with the parent present, and the parent will provide verbal consent on behalf of the child. For these cases, we request a waiver of documentation of consent/assent for parents and children based on the following considerations: (i) participating in the study constitutes "no more than minimal risk"; (ii) the rights and welfare of the subjects will not be adversely affected, since parents and children will be given all elements of informed consent both in writing and verbally over the phone; (iii) increased study feasibility: we would like to minimize the burden that may result from returning a consent form via mail or email. Once a participant signs the consent, the RC will register participant in PediQUEST web, assign study status as "enrolled participant," create the corresponding PQ accounts as explained in 2.5, manually assign the Baseline Packet and baseline PediQUEST Surveys, and email the patient's primary oncology team. Study identification numbers have been generated by the Study data center and are embedded in each site's pool list. All participants will be registered in DFCI's Clinical Trial Management System Oncore following

procedures specified in DF/HCC SOPs REGIST-101 and REGIST-104. Randomization procedures are explained in the next section.

Strategies to enhance recruitment include a direct family approach, flexibility in scheduling recruitment interviews, and working with experienced RCs (in at least two of the sites the RCs have already worked in prior or related projects of this group). Some study characteristics such as its relatively short duration, facilitation of PediQUEST web's registration process by the RC, and the small non-monetary incentives provided (section 2.3.2), should also boost recruitment and retention rates. Finally, the advertising and in-service sessions with providers should help reduce any potential barriers to identify/refer patients to the study.

Should a participant reach the age of majority while participating in the study, study interventions will continue. We are requesting a waiver of documentation of consent for these patients given the consent documents and study procedures for adolescents and young adults are identical and adolescents must provide assent to participate. The continued collection of data during this period presents no more than minimal risk, and halting study procedures would likely lead to loss of valuable study data. An information sheet (appendix) which contains all elements of informed consent will be provided to participants who reach the age of majority at the earliest opportunity. If the participant is not scheduled for a clinic visit within a month of their birthday, the RC will call to review the sheet over the phone.

With the purpose of studying selection bias, and understand better the characteristics of the enrolled sample, i.e. how well enrolled patients represent the pool of eligible patients, we will collect vital status (Dead/Alive) at 6 months of all patients identified as eligible. For deaths of patients who were randomized, we will also collect date of death as it will be used in the exploratory analysis. We will also collect information on race, ethnicity, and English proficiency of all approachable families, including those that decline participation. Families that decline participation will be asked four structured questions on their race, ethnicity, and English proficiency and two brief open-ended questions to understand their reasons for non-participation and whether virtual methods constitute a barrier to participation (see Non-Participation Survey). These questions will be asked during the approach or emailed to families no later than 3 days after a declination or opt out. Families will be reminded that they can decline to answer any questions.

